## Abstract

**Background:**

Combined allergic rhinitis and asthma syndrome (CARAS) is a prevalent chronic respiratory disorder among children, characterized by the coexistence of allergic rhinitis and asthma symptoms, thereby substantially impairing quality of life. Pediatric Tuina, a traditional Chinese manual therapy, has demonstrated potential in the management of pediatric respiratory conditions; however, its effectiveness in treating CARAS remains insufficiently studied.

**Objective:**

This trial aims to assess the clinical efficacy and safety of pediatric Tuina in the treatment of CARAS, with the objective of establishing an effective, safe, and convenient external therapy of traditional Chinese medicine for CARAS.

**Methods:**

A total of 92 children aged 6–14 years with CARAS in remission will be randomly assigned (1:1) to either the control group (conventional medication) or the intervention group (conventional medication plus pediatric Tuina). The intervention will be administered three times weekly for 4 weeks, followed by a 24-week follow-up. The primary outcome measure is the Pediatric Rhinoconjunctivitis Quality of Life Questionnaire (PRQLQ) score. Secondary outcomes include the Childhood Asthma Control Test (C-ACT) / Asthma Control Test (ACT) score and traditional Chinese medicine (TCM) symptom scores. Safety will be assessed by monitoring any adverse events during the treatment period.

**Discussion:**

This study will provide evidence for the efficacy and safety of pediatric Tuina in improving CARAS symptoms and quality of life in children.

**Clinical trial registration:**

https://itmctr.ccebtcm.org.cn/mgt/project/view/1966089236985806848, identifier [ITMCTR2025001712].

## Introduction

1

### Background

1.1

Combined allergic rhinitis and asthma syndrome (CARAS) is a syndrome characterized by concurrent allergic rhinitis (AR) and asthma, sharing standard pathophysiological mechanisms involving IgE-mediated hypersensitivity and immune dysregulation (1, 2). Allergic rhinitis and asthma are common inflammatory diseases of the airways that frequently coexist, a condition sometimes referred to as “united airway disease” (3). Epidemiological studies have consistently shown a strong association between the two conditions, with allergic rhinitis often preceding the development of asthma (4, 5). The prevalence of allergic rhinitis in patients with asthma is high, with estimates ranging from 80% to 90% (4). One study of 142 asthma patients in Tianjin, China, found that 68% also had allergic rhinitis (5). In a broader survey in Shenmu City, China, the prevalence of allergic rhinitis was 25.4%, and asthma was 9.4%, with 6.5% of the adult population having combined allergic rhinitis and asthma (6). Another study involving 650 asthma patients found that 85% had concomitant allergic rhinitis (7). A meta-analysis shows that in China, the comorbidity rate of AR and asthma in children is substantial, with 35.01% of AR children developing asthma and 54.93% of asthmatic children experiencing AR (8). Globally, among children, the estimated prevalence of asthma is 12.0% and of allergic rhinitis is 12.7% (9). CARAS in children leads to recurrent nasal symptoms (e.g., congestion, sneezing) and lower respiratory symptoms (e.g., wheezing, cough), affecting sleep, school performance, and long-term quality of life (10).

Current management of CARAS primarily relies on pharmacotherapy, such as montelukast and inhaled corticosteroids, which may be associated with adverse effects (e.g., growth suppression) and poor long-term adherence (11). Thus, safe and effective complementary therapies are urgently needed.

Pediatric Tuina, a non-pharmacological therapy rooted in Traditional Chinese Medicine (TCM), involves stimulating specific acupoints to regulate qi (vital energy) and blood circulation. It has been used to treat pediatric respiratory conditions, with studies showing efficacy in reducing symptoms of AR and asthma (12–17). For example, a randomized trial demonstrated that pediatric Tuina improved nasal symptoms in children with mild AR, with better long-term effects than loratadine (14). Another study reported that Tuina combined with medication reduced asthma exacerbations and improved lung function in children (17). However, no rigorous trials have specifically evaluated Tuina for CARAS. In summary, as a common chronic inflammatory airway disease in children, the current conventional treatment for CARAS is associated with long-term dependency and limitations. Pediatric Tuina massage, as a non-pharmacological adjuvant therapy, has shown promise for treating isolated allergic rhinitis or asthma. However, systematic research on its holistic efficacy, standardized protocols, and mechanisms of action for CARAS as a comorbid condition remains insufficient. This study aims to conduct a randomized controlled trial to test the following hypothesis: pediatric massage combined with conventional treatment is more effective than traditional treatment alone in controlling the comprehensive symptoms and improving the quality of life of children with CARAS. The findings of this study are expected to provide high-level evidence for a safe and effective non-pharmacological Traditional Chinese Medicine intervention in the clinical management of CARAS.

### Objectives

1.2

Primary objective: to assess the clinical efficacy and safety of pediatric Tuina as an adjunctive therapy for children with CARAS in the remission phase.

Secondary objectives: to evaluate improvements in quality of life (PRQLQ), asthma control (C-ACT/ACT), TCM symptom scores, and safety profiles.

## Methods

2

### Study design

2.1

This is a single-center, randomized, superiority, parallel-group controlled trial with a 1:1 allocation ratio. This is a single-center trial. All participant recruitment, intervention, and assessment procedures will be conducted at the Shanghai Municipal Hospital of Traditional Chinese Medicine, Shanghai, China. The study will consist of a 4-week intervention phase and a 24-week follow-up phase. Outcome assessments shall be conducted at baseline (T0), following the intervention (T1, week 2; T2, week 4), and during follow-up periods (T3, week 8; T4, week 12; T5, week 28). Assessors will remain blinded to group allocation to mitigate potential bias.

Table 1 presents the study schedule.

**Table 1 T1:** Timeline for the study protocol.

	Trial period						
	Enrollment		Post-randomization		Follow-up		Close-out
Timepoint	–T1 to T0	T0	T1	T2	T3	T4	T5
Enrollment	
Eligibility screen	X						
Informed consent	X						
Randomization		X					
Intervention or comparator							
Intervention group: conventional medication plus pediatric Tuina		X	X	X			
Comparator group: conventional medication		X	X	X			
Assessments							
Baseline		X	X	X	X	X	X
PRQLQ		X	X	X	X	X	X
C-ACT/ACT		X	X	X	X	X	X
TCM symptom scores		X	X	X	X	X	X
Safety evaluation		X	X	X			

PRQLQ, pediatric rhinoconjunctivitis quality of life questionnaire; C-ACT, childhood asthma control test; ACT, asthma control test.

### Participants

2.2

#### Inclusion criteria

2.2.1

a) Meeting the diagnostic criteria of Western medicine and TCM as specified in the “Expert Consensus on Integrated Traditional Chinese and Western Medicine Diagnosis and Treatment of Allergic Rhinitis-Asthma Syndrome” (10);b) The disease is in remission stage;c) Aged 6–14 years;d) The child's guardian has formally signed the informed consent form.e) Children aged 8 years and above have provided their informed consent by signing the appropriate form.

#### Exclusion criteria

2.2.2

a) Patients experiencing nasal congestion and rhinorrhea attributable to acute rhinitis, vasomotor rhinitis, among other conditions.b) Children with congenital nasal physiological abnormalities, such as nasal stenosis, deviated nasal septum, adenoid hypertrophy, and others.c) Patients experiencing wheezing discomfort due to bacterial bronchitis, bronchial developmental malformations, airway foreign bodies, respiratory failure, bronchiectasis, chronic obstructive pulmonary disease, among other conditions.d) Children with primary diseases such as cardiovascular, cerebrovascular, hepatic, renal, and hematopoietic system conditions.e) Children participating in other research groups;f) Individuals unable to cooperate with the treatment.g) Ulcers, infections, or skin lesions at the acupoint application sites.

#### Withdrawal criteria

2.2.3

Voluntary withdrawal by caregivers or participants.Severe adverse events or exacerbation of CARAS necessitating emergency treatment.Failure to comply with at least 30% of interventions or assessments.

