#### Control group: conventional medication

2.5.1

Participants will receive montelukast sodium chewable tablets: 5 mg once daily (bedtime).

Acute exacerbations during the trial will be managed with salbutamol aerosol or budesonide plus terbutaline nebulization, in accordance with clinical guidelines.

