#### Safety outcome

2.6.3

Adverse events (AEs) will be continuously monitored. Participants will be explicitly asked about any new or worsening symptoms at each treatment session and follow-up assessment. AEs specifically related to pediatric Tuina include, but are not limited to: intolerable pain, skin irritation, hematoma, bleeding, skin allergy, sweating, syncope, or dizziness. All AEs occurring during the trial will be assessed and documented in case report forms. Investigators will record detailed information on treatment measures, extent, duration, and the date of the AE. In the event of a serious AE, investigators must report it to the Ethics Committee of Shanghai Municipal Hospital of Traditional Chinese Medicine. The Ethics Committee will decide whether to withdraw a participant experiencing an AE, and will conduct audits every three months.

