### Data collection and management

2.7

Data will be recorded on case report forms (CRFs) and double-entered into an encrypted database. Missing data will be handled using multiple imputation. A Data Safety Monitoring Board will review data for safety and adherence to protocols. All electronic data will be stored using industry-standard encryption technology to prevent unauthorized access and data breaches. We will strictly control data access permissions to ensure that only authorized research team members can access this data, and passwords will be subject to regular audits to protect all access activities.

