### Statistical analysis

2.9

All statistical analyses will be performed using Python (version 3.10 or higher). Data analysis will be conducted using standard scientific computing libraries, including NumPy, pandas, SciPy, and statsmodels. Data distribution will be assessed using the Shapiro–Wilk test. Normally distributed continuous variables will be presented as mean ± standard deviation (SD), while non-normally distributed data will be summarized as median with interquartile range (IQR). Categorical variables will be expressed as frequencies and percentages. A two-sided *p* value < 0.05 will be considered statistically significant.

All analyses will be conducted according to the intention-to-treat (ITT) principle, including all randomized participants in the groups to which they were originally assigned. A per-protocol (PP) analysis will also be performed including participants who complete the intervention without major protocol deviations. Safety analyses will include all participants who receive at least one session of the assigned intervention.

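### The withdrawal criteria do not separate stopping treatment from leaving the study, so data may go missing for reasons tied to disease course and adherence, and the 30% compliance rule has two readings

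*Protocol article*

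**What the plan says.** Besides voluntary withdrawal, section 2.2.3 (Withdrawal criteria) gives two triggers: "Severe adverse events or exacerbation of CARAS necessitating emergency treatment" and "Failure to comply with at least 30% of interventions or assessments". It does not say what happens to later assessments.

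Three other parts of the article bear on this:

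- **Exacerbations and adverse events.** Section 2.5.1 says "Acute exacerbations during the trial will be managed with salbutamol aerosol or budesonide plus terbutaline nebulization, in accordance with clinical guidelines", with no mention of withdrawal. Section 2.6.3 (Safety outcome) says "The Ethics Committee will decide whether to withdraw a participant experiencing an AE".
- **Analysis sets.** Section 2.9 promises intention-to-treat analysis, "including all randomized participants in the groups to which they were originally assigned". It adds a second set: "A per-protocol (PP) analysis will also be performed including participants who complete the intervention without major protocol deviations".
- **Missing data.** Section 2.7 says "Missing data will be handled using multiple imputation".

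**The concern.** A serious exacerbation is part of the disease course that the trial measures. If such a child leaves the study, the poor scores that would have followed are never recorded. Multiple imputation under the usual missing-at-random assumption recovers them only as far as the child's earlier data predict them. The asthma control and symptom scores are hit most directly. PRQLQ is hit less directly, because the Discussion states that it does not cover the asthma component.

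Withdrawal for poor compliance raises a related problem. Intention-to-treat analysis is meant to keep such children under observation, and the per-protocol set in section 2.9 already deals with them. Withdrawing them does the per-protocol set's work at the data-collection stage, where it cannot be undone.

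The trigger for withdrawal after an exacerbation is also undefined. Nothing separates an exacerbation managed within the trial from one that counts as an emergency. Section 2.4 leaves the recruiting and treating investigators unblinded, so a loose trigger could be applied differently in the two arms.

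**Working it through.** **1. Does withdrawal mean leaving the study?** Section 2.2.3 does not say. The compliance threshold covers assessments as well as interventions, and a rule triggered by missed assessments makes little sense if it only stops treatment. Leaving the study is therefore the more natural reading, but it remains an inference.

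**2. How the rules fit together.** Section 2.2.3 covers only exacerbations that need emergency treatment, and section 2.5.1 covers acute exacerbations in general. Both can apply to the same child, and no boundary is given. For severe adverse events, section 2.2.3 lists a withdrawal criterion, while section 2.6.3 leaves the decision to the Ethics Committee.

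**3. The two readings of the 30% rule.** Section 2.5.2 gives 3 sessions a week for 4 weeks, so 3 × 4 = 12 sessions, and 30% of 12 is 3.6.

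- Reading A, withdrawn if compliance is below 30%: fewer than 3.6 sessions attended, so 3 or fewer.
- Reading B, withdrawn if 30% or more is missed: at least 3.6 missed, so 4 or more missed and 8 or fewer attended.

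A child attending 4 to 8 sessions stays under A and is withdrawn under B. There are five post-baseline assessments (T1 to T5). Under B, missing two of them (2/5 = 40%) triggers withdrawal, so partly missing data could become wholly missing from then on.

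**4. Exposure by arm.** Both arms take daily medication and attend the same assessments, so the rule reaches both. Only the Tuina arm has 12 sessions to miss, so it is more exposed.

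**5. Scale.** Section 2.3 uses δ = 10 and σ = 8.21. Its sample size reproduces:

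- 2 × [(1.96 + 1.28) × 8.21/10]² = 14.15, rounded up to 15
- 15/0.4 = 37.5, rounded up to 38
- 38 × 1.2 = 45.6, rounded up to 46 per group

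That figure is not in dispute here. It supplies δ and σ as yardsticks.

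**6. Illustrative shift in PRQLQ.** The article gives no withdrawal or exacerbation rate by arm, so the rates below are assumptions.

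Shift = (difference in withdrawal proportion) × (mean PRQLQ excess that imputation misses, taken as equal in both arms)

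- 0.05 × 10 = 0.5 points, or 5% of δ
- 0.10 × 10 = 1.0 points, or 10% of δ
- equal proportions: 0

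**7. An upper-end variant.** Suppose the children lost are exactly those with the worst PRQLQ scores, and imputation reproduces only the mean of those who remain. For a normal outcome, losing the worst fraction q lowers an arm's mean by σ·φ(z₁₋q)/(1 − q). With σ = 8.21 this is 0.89 for q = 5%, 1.60 for 10% and 2.87 for 20%.

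| Assumed loss, control vs Tuina | Shift in difference (points) |
|---|---|
| 10% vs 5% | 0.7 |
| 20% vs 10% | 1.3 |
| 20% vs 5% | 2.0 |
| equal | 0 |

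Higher PRQLQ is worse. Greater loss among controls therefore shifts the result toward no difference, and greater loss in the Tuina arm shifts it in favour of Tuina.

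**The case against.** The strongest reply is that a condensed article need not describe what follows withdrawal. The full protocol may say that assessments continue, and the imputation model belongs in the analysis plan. The second half stands: the missing imputation details are not criticised here. The first half stands in part, because loss of data is inferred rather than stated. But section 2.2.3 states a rule, and that rule, followed as written, most naturally removes children from the study.

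A reader might also infer stronger things that the text does not support:

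- **That sections 2.2.3 and 2.5.1 contradict each other.** They overlap without a boundary.
- **That the intention-to-treat statement is contradicted.** Section 2.9 keeps every randomised child and section 2.7 imputes missing values. The analysis is weakened, not denied.
- **That compliance withdrawal affects the Tuina arm alone.** The rule covers both arms, with unequal exposure.
- **That values would be imputed only from children without exacerbations.** Children whose exacerbations are managed in the trial stay in, and a withdrawn child's earlier scores can inform the imputation.
- **That the shift is 12.5% to 25% of the planned effect.** This needs an effect of 4 points (0.5/4 and 1.0/4). Section 2.3 states 10 and divides the sample size, not the difference, by 0.4.

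The 10-point excess has no source in the article. It may be high for PRQLQ, given that questionnaire's limited scope.

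**Conclusion.** The point holds in a limited form. As written, section 2.2.3 ties withdrawal to disease course and adherence, does not protect later outcome assessment, and sets a compliance threshold that two readers would apply differently to any child attending 4 to 8 of 12 sessions. If withdrawal ends assessment, the intention-to-treat comparison depends on imputation for the children whose outcomes are hardest to predict.

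The two readings of the threshold follow from the article's own figures. The bias does not: its size and direction cannot be computed. The 0.5 to 1.0 points rest on assumed rates and an assumed excess, and the 0.7 to 2.0 points on a deliberately severe loss pattern. All are modest against a difference of 10 and vanish if the arms lose equally. The case for change is that uncollected data cannot be recovered later and that prevention is cheap.

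**What to change.** - In section 2.2.3, separate stopping treatment from leaving the study. State that PRQLQ, C-ACT/ACT and TCM symptom scores continue to T5 for every randomised child unless consent is withdrawn, and that observed values enter the intention-to-treat analysis.
- Remove non-compliance as a ground for withdrawal. Use it only to define the per-protocol set, in one form with one meaning, such as attendance at no fewer than a stated number of the 12 sessions.
- Reconcile sections 2.2.3, 2.5.1 and 2.6.3 on when an exacerbation or severe adverse event leads to withdrawal, and who decides. The clinical rule itself is for the investigators and the Ethics Committee.
- Optionally, add a sensitivity analysis that imputes worse values after an exacerbation.

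The cost is some rewording and some effort to retain these families. The visits are already scheduled in Table 1, so none is added.

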### Sample size calculation

2.3

The sample size was calculated based on the primary outcome (PRQLQ). Based on previous literature (18), we assumed a minimal clinically significant difference of 10 points in PRQLQ between groups to ensure a more conservative estimate of statistical power.

The sample size was estimated using the formula for comparing means between two independent samples:

$$\begin{array}{c} \text{n}=2\times {\left[\left(\text{Z}1-\text{α}{/}_{2}+\text{Z}1-\text{β}\right)\times \text{ σ}/\text{δ}\right]}^{2} \end{array}$$

Given:

$$\begin{array}{l} \text{ δ}=10,\text{σ}=8.21,\text{Z}1-\text{α}{/}_{2}=1.96\left(\text{α}=0.05\right),\\ \text{Z}1-\text{β}=1.28\left(\text{β}=\;0.1\right) \end{array}$$

Substituting these values yielded –*n* = 15 per group.

However, considering that the reference study used conventional treatment + Chinese herbal medicine + tuina therapy in the experimental group, while this study uses only conventional treatment + tuina (without herbal medicine), it was estimated that 60% of the effect in the reference study was attributable to herbal medicine and 40% to tuina. Therefore, the sample size was adjusted to^*^*n* = 15 ÷ 0.4 ≈ 38 per group.

Accounting for a potential dropout rate of ≤ 20%, the adjusted sample size was calculated as:

$$\begin{array}{c} {\text{n}}_{\text{adjusted}}=38\times 1.2\;\approx \;46\text{ per group}. \end{array}$$

The final sample size was set at 46 participants per group, for a total of 92, to ensure balanced baseline characteristics between groups.

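### The 40% effect share is applied to the sample size instead of the difference, so 38 per group has about 55% power for the implied 4-point effect, not 90%

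*Protocol article*

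**What the plan says.** The whole calculation is in section 2.3 (Sample size calculation) of the protocol article.

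- **Target difference.** The authors write that "we assumed a minimal clinically significant difference of 10 points in PRQLQ between groups", citing earlier literature.
- **Method.** "The sample size was estimated using the formula for comparing means between two independent samples". The formula shown is n = 2 × [(Z for alpha + Z for beta) × sigma/delta]², with delta = 10, sigma = 8.21, Z values 1.96 and 1.28, and a result of 15 per group.
- **Adjustment.** The reference study gave herbal medicine as well as Tuina, and this trial gives Tuina without herbs. For that reason "it was estimated that 60% of the effect in the reference study was attributable to herbal medicine and 40% to tuina". The share is applied as "15 ÷ 0.4 ≈ 38 per group".
- **Dropout.** An allowance of up to 20% is applied as 38 × 1.2, giving 46 per group and 92 in total.

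Section 2.9 (Statistical analysis) confirms two-sided testing: "A two-sided *p* value < 0.05 will be considered statistically significant". Section 2.1 gives 1:1 allocation.

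**The concern.** The adjustment is justified by a smaller expected effect but is carried out on the number of patients. In the formula printed just above it, n is inversely proportional to the square of the difference, so cutting the effect to 40% and dividing n by 0.4 are not the same operation. The division is far too small a correction for the reason given.

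The 10 points also has two roles that cannot both hold. It is introduced as a minimal clinically significant difference, which does not shrink because a treatment component is dropped. It is then treated as the effect of a combined treatment, of which Tuina contributes a part.

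This is the only justification given for enrolling 92 children on the primary outcome. If the assumed Tuina effect is real but the power is near 55%, a null result is almost as likely as a positive one and could be read as evidence that Tuina does not work. Conversely, a significant difference of 4 to 6 points would fall well short of what the article itself calls the minimal clinically significant difference.

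**Working it through.** **Inputs** (section 2.3 unless noted): delta = 10 PRQLQ points; SD = 8.21; two-sided alpha = 0.05, Z = 1.96 (also section 2.9); beta = 0.1, Z = 1.28; Tuina share of effect = 0.4; 1:1 allocation (section 2.1); dropout up to 20%.

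**1. Reproduce the article's figures.**

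- n = 2 × [(1.96 + 1.28) × 8.21/10]² = 2 × (2.660)² = 14.15, rounded up to 15.
- 15/0.4 = 37.5, rounded to 38.
- 38 × 1.2 = 45.6, rounded to 46.

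All three stated figures reproduce. The error is in the choice of operation at the second step.

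**2. Apply the 40% where the formula needs it.** Implied difference: 0.4 × 10 = 4 points.

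- n = 2 × [(1.96 + 1.28) × 8.21/4]² = 2 × (6.650)² = 88.4, so 89 per group evaluable (90 with the t distribution).
- The multiplier on n is 1/0.4² = 6.25. The article used 1/0.4 = 2.5.
- With dropout: 89 × 1.2 = 106.8, so 107 per group by the article's method; 89/0.8 = 111.25, so 112 if 89 are to remain after a 20% loss.

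**3. What dividing n by 0.4 actually assumes.** Since n is proportional to 1/delta², multiplying n by 2.5 corresponds to delta = 10 × √0.4 = 6.3 points. That keeps 63% of the effect, a share that section 2.3 does not state.

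**4. Power of the planned size** (two-sample t-test, SD 8.21, two-sided 0.05):

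| Evaluable per group | Power for 4 points | Difference with 90% power |
|---|---|---|
| 36 | 53% | 6.4 points |
| 37 | 54% | 6.3 points |
| 38 | 55% | 6.2 points |
| 46 (no dropout) | 64% | 5.6 points |

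The rows for 36 and 37 are included because 46 × 0.8 = 36.8: multiplying by 1.2 does not fully protect 38 evaluable per group at 20% loss. Dividing 38 by 0.8 would give 48. That is a minor point beside the main one.

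The normal approximation gives 56.5% at 38 and 64.7% at 46, so the method of calculation does not matter here.

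**5. The other reading.** If 10 points is the target for Tuina itself, no scaling applies, 15 per group is the answer to the formula, and 38 per group has power above 99%.

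**The case against.** The strongest reply is that the 4-point figure is inferred. Section 2.3 never writes delta = 4. It assigns 40% of the reference study's effect to Tuina, and that effect is not reported. The 10 points is described as a conservative choice, so the observed effect may have been larger. With 38 per group and SD 8.21, power would be about 55% if the reference effect was 10 points (Tuina 4.0), about 71% if it was 12 (Tuina 4.8), and about 90% if it was about 15.5 (Tuina 6.2). This caveat stands, and the 55% should be read as conditional on the 10-point base. It does not rescue the step: the 0.4 was applied to an n built on delta = 10, no larger effect is stated, and dividing n by 0.4 would be the wrong operation whatever the reference effect was.

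Second, beta = 0.1 is attached to the n = 15 step, and power is not restated for 38 or 46. That is true, but the later steps are presented as adjustments to that calculation, with no sign that the power target was dropped.

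Third, 55% is near the low end. Less dropout, or adjustment for baseline PRQLQ, would help. With all 46 evaluable, power for 4 points is 64%. Assuming a baseline correlation of 0.5 (not in the article), adjustment would give about 68% at 38 per group and 76% at 46. All remain short of 90%.

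Finally, a significance threshold below the design difference is normal in an adequately powered trial and is not an error. I do not count it as one.

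**Conclusion.** The concern holds. The article's arithmetic reproduces, but the adjustment is invalid under its own formula and nothing elsewhere in the document repairs it. Taking the 40% at face value on the 10-point base, the trial needs 89 evaluable children per group for 90% power and plans for 38. The power for the implied 4-point effect is about 55%, so the chance of missing it is about 45% instead of the stated 10%. This rests on SD 8.21, a two-sided 0.05 test, an unadjusted comparison and a reference effect of 10 points. If 10 points is the target for Tuina alone, the trial has over 99% power and the adjustment has no basis. Neither reading makes 38 per group the size for 90% power, and the article must say which one it means. This should be corrected, because it is the sole stated basis for the sample size on the primary outcome.

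**What to change.** 1. State what the 10 points is: a minimal important difference, or the effect seen in the reference study. Report the reference study's observed difference and the basis for the 40% share.
2. Delete the step that divides 15 by 0.4.
3. Either re-size for the effect actually assumed (89 evaluable per group if that is 4 points, before dropout), or keep 92 children and state what they deliver. Suggested wording for the second option: *With 38 evaluable children per group and an SD of 8.21, the trial has 90% power to detect a PRQLQ difference of 6.2 points and about 55% power for a difference of 4 points (two-sided 5% level, unadjusted comparison).* If this is used, say why 6.2 points is a plausible and relevant effect, so that it is not simply fitted to the number already chosen.
4. Optionally, commit to interpreting the confidence interval for the PRQLQ difference against the 10 points, if that remains the clinical threshold.

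**Cost.** Keeping 92 needs only a rewrite of section 2.3, and of the registration entry if it carries the same justification. No patients are added and treatment is unchanged; the stated power simply becomes less favourable. Re-sizing for 4 points would raise enrolment from 46 to about 107 to 112 per group, depending on how dropout is applied.

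### The dropout allowance multiplies 38 by 1.2 instead of dividing by 0.8, so 46 per group does not leave 38 evaluable at 20% dropout

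*Protocol article*

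**What the plan says.** Section 2.3 (Sample size calculation) builds the sample size in three steps.

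1. A two-sample comparison of means with a "minimal clinically significant difference of 10 points in PRQLQ between groups", an SD of 8.21, two-sided α of 0.05 and β of 0.1 gives 15 per group.
2. That number is divided by 0.4, the share of the reference study's effect credited to Tuina: "15 ÷ 0.4 ≈ 38 per group".
3. Attrition is added: "Accounting for a potential dropout rate of ≤ 20%, the adjusted sample size was calculated as" 38 multiplied by 1.2, which is rounded to 46 per group.

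The section concludes: "The final sample size was set at 46 participants per group, for a total of 92". It gives no other reason for the factor 1.2. Its closing remark about balanced baseline characteristics does not explain the factor.

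**The concern.** An allowance for dropout should ensure that the required number remains after the stated loss. Dropout is a fraction of the children randomised, not of the children who remain. Multiplying by 1.2 adds 20% of the evaluable target, which is less than 20% of the enrolled number. The plan therefore says that 46 per group protects a target of 38 against losses of up to 20%, and by its own figures it does not.

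At stake is the accuracy of a printed property of the design. PRQLQ is collected up to week 28 (sections 2.1 and 2.6.1), and the withdrawal criteria in section 2.2.3 include exacerbation needing emergency treatment and poor compliance. Losses in the upper part of the stated range are therefore possible.

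**Working it through.** **Inputs** (section 2.3 unless stated): δ = 10, σ = 8.21, z-values 1.96 and 1.28, scaling factor 0.4, dropout up to 20%, 1:1 allocation (section 2.1). Section 2.9 confirms the two-sided 0.05 level.

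**The plan's figure reproduced**
- n = 2 × [(1.96 + 1.28) × 8.21 / 10]² = 14.15, rounded up to 15.
- 15 / 0.4 = 37.5, rounded up to 38.
- 38 × 1.2 = 45.6, rounded up to 46, so 92 in total.

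Every printed number is recovered, so 46 comes from n × (1 + d), where d is the dropout proportion.

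**The inflation that matches the stated aim**
- To retain n after losing a proportion d, enrol n / (1 − d).
- 38 / (1 − 0.20) = 47.5, so 48 per group and 96 in total.
- Check: 48 × 0.8 = 38.4, which is at least 38.

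**What 46 delivers**
- At 20% dropout: 46 × 0.8 = 36.8 per group; over both groups, 92 × 0.8 = 73.6 against 2 × 38 = 76.
- In whole children: losing 8 leaves 38 (8/46 = 17.4%) and losing 9 leaves 37 (9/46 = 19.6%). A group that loses 10 has 36; with 8 lost in the other group, overall dropout is 18/92 = 19.6%, still within the limit.
- Highest dropout that keeps 38: 1 − 38/46 = 17.4%.

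**Effect on power**, using the plan's normal approximation, power = Φ(δ / (σ√(2/n)) − 1.96):

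| Evaluable per group | δ = 10 × √0.4 ≈ 6.3 | δ = 10 × 0.4 = 4 |
|---|---|---|
| 38 | 0.919 | 0.565 |
| 37 | 0.912 | 0.554 |
| 36 | 0.905 | 0.543 |

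The 6.3-point column is the effect implied by dividing n by 0.4, because n is proportional to 1/δ². The 4-point column reads the 40% share as applying to the effect itself. Falling from 38 to 37 or 36 costs 0.7 to 1.4 percentage points in the first case and 1.1 to 2.2 in the second.

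**The case against.** The best defence is that 38 was itself rounded up twice. Carried without rounding, 14.15 / 0.4 = 35.4 per group, and 35.4 / 0.8 = 44.2, so 45 per group would cover 20% dropout at 90% power, and 46 exceeds that. The arithmetic is right, and it explains why the 90% target is not lost at a 6.3-point effect. It is not the plan's route, though: the plan fixes 15, then 38, and inflates 38. Removing only the second rounding does not rescue 46, since 37.5 / 0.8 = 46.9, or 47 per group.

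A second defence is that the analysis is by intention to treat (section 2.9) with multiple imputation (section 2.7), so a child lost late is not simply subtracted and 36.8 is a worst case. This has some force. But imputation does not in general restore all the information lost with missing outcomes, and the per-protocol analysis excludes children who do not complete the intervention. Having chosen to inflate for dropout, the plan should do so correctly.

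A third is that the limit is worded as at most 20%. An allowance stated as an upper limit has to hold at that limit, and this one fails above 17.4%.

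Finally, the division by 0.4 in the same section is open to challenge on its own account, and changing it would replace 38 altogether. That is so, but it is a separate matter. It neither causes nor cures the error in the dropout step.

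**Conclusion.** The concern holds. Taking the plan's own requirement of 38 evaluable per group and its own 20% limit, 46 per group is too few: the matching figure is 48 (96 in total), a difference of 2 per group and 4 overall. At 20% dropout about 37 per group remain, a shortfall of one to two children.

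The consequence is minor. Power falls by about 1 to 2 percentage points, and at the 6.3-point effect implied by the plan's scaling it stays above 0.90. The false statement is the dropout cover, which is about 17% and not 20%. These figures assume that children who drop out contribute nothing to the primary comparison, and they take 38 as given without endorsing the step that produced it.

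**What to change.** Correct the line in section 2.3 in one of these ways:

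- keep 92 and state that the sample size allows for up to 17% dropout; or
- keep 92, state that 20% dropout leaves about 37 per group, and give the power for that number together with the effect size assumed.

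Either costs one line of text and no additional children. If the sponsor wants 38 evaluable per group guaranteed at 20% dropout, enrol 48 per group (96 in total), which is 4 more children.

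If the 0.4 scaling is revised and the target of 38 changes, the new target should be divided by 0.8, not multiplied by 1.2. Correcting the dropout step alone does not settle whether 38 is the right target.
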